## Data Management

### Data collection instruments

Study data will be entered directly into specialized data collection software on electronic tablets by study staff, with a unique identifier automatically generated at the time of subject enrollment. A unique electronic form will be created for each questionnaire listed above. The key for linking records will be stored electronically in a password protected database. See “Data Security” for additional details. On a daily basis, databases will automatically be backed up to a second secured server at a different geographic location than the primary project server.

### Data monitoring dashboard

A dashboard will track and visualize key quality control metrics in real time that will include (i) facility specific enrollment, (ii) patient follow-up measures, (iii) questionnaire completeness, (iv) chronic COVID-19 symptom monitoring, (v) withdrawal and loss to follow-up. By monitoring the collection and processing of data in real time, we will be able to quickly identify and address issues that may arise during the project.

## Sample size for primary outcome indicators

To calculate the power to detect a difference between two specific groups, we used a two-sided test of independent proportions with the statistical parameters of alpha 0.05, beta 0.2, and power of 0.8. The intervention effect was selected to provide clinically and operationally meaningful outcomes. In addition, the power calculations are based on the following assumptions.

- Likelihood of referral for higher care: According to a study on the use of pulse oximeters to determine referral of COVID-19 patients to a higher level of care, 24.7% of patients required such a referral, in a second study 33% of patients using a pulse oximeter at home and receiving remote COVID-19 management were referred. Given that those studies were conducted prior to the availability of vaccines, and 34% of the Honduran population is vaccinated, we will use a baseline estimate that 20% of patients will be referred for higher care, with a greater proportion referred in the group using pulse oximeters, given additional opportunities to detect the need for referral. The ability to detect a 6% absolute difference between referral rates between arms requires an enrollment of 804 patients per arm for a total enrollment of 1,608 participants.
- Likelihood of hospitalization: The most recent published COVID-19 study in Honduras identified a 25% hospitalization rate in the general population, prior to vaccine availability. We estimate that 10% of all enrolled patients will be hospitalized, taking into account increasing vaccination coverage and the high risk status of the enrolled population. The ability to detect a 5% absolute difference in hospitalization rates between arms requires 946 participants per arm for a total enrollment of 1,892 participants.
- Length of hospitalization: Given an average of 7.7 days hospitalization per admitted patient (SD 10.8), a per arm/strategy sample size of 773 is powered to detect a 20% difference in length of hospitalization between groups for a total enrollment of 1546 participants.
- Pulse oximetry: Given an estimated mean SpO2 of 93% (SD 7%) at the time of evaluation at a higher level of care, a per arm/strategy sample size of 85 is powered to detect an absolute difference between groups of SpO2 of 3%, for a total of 255 patients referred to a higher level of care, for a total enrollment of 850 participants.
- Mortality: Given an estimated mean mortality of 7.5% among the enrolled population, a per arm sample size of 854, and a total sample of 1708, is powered to detect a difference in mortality rate of 3.3% between groups. The mean mortality rate among people with COVID in Honduras is 2.8% among the general population. Given that the enrolled population will be older and more likely to live with comorbidities for negative COVID outcomes, a higher estimated mortality rate has been used.

| Covariate                                                 | General population (SD) |
|-----------------------------------------------------------|-------------------------|
| Proportion of COVID-19 patients requiring hospitalization | 25%                     |
| Duration of hospitalization                  | 7.7 days (10.8)         |
| SpO2 at time of evaluation at higher level of care        | 93% (7%)                |

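### The hospitalization sample size of 946 per arm (1,892 in total) does not follow from the 10% rate, 5-point difference, two-sided 0.05 level and 80% power stated for it

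*Protocol*

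**What the plan says.** All of this is in the protocol section on sample size for the primary outcome indicators.

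- The opening sentence sets one method for the group comparisons: a "two-sided test of independent proportions with the statistical parameters of alpha 0.05, beta 0.2, and power of 0.8".
- The hospitalization bullet gives the event rate: "We estimate that 10% of all enrolled patients will be hospitalized".
- The same bullet gives the effect and the result: to "detect a 5% absolute difference in hospitalization rates between arms requires 946 participants per arm for a total enrollment of 1,892 participants".
- The referral bullet assumes 20% at baseline with more referrals in the oximeter group. A 6-point difference "requires an enrollment of 804 patients per arm for a total enrollment of 1,608 participants".
- The mortality bullet assumes 7.5% and a 3.3-point difference, with 854 per arm (1,708 in total).

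The five totals listed are 1,608, 1,892, 1,546, 850 and 1,708. None is named as the enrolment target. The hospitalization bullet does not say whether the rate is expected to rise or fall, and gives no allowance for dropout or multiplicity. Admission is part of the disposition-after-referral indicator, which the Indicators section marks as primary.

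**The concern.** A sample size statement should be reproducible from its own inputs. Two of its neighbours can be rebuilt to within a patient or two with a single standard formula. The hospitalization figure cannot, and the gap is far too large for rounding or choice of software.

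This is also the largest of the five totals. If the largest total were used to plan enrolment, this figure would set it, and a reader would take the trial to have 80% power for a 5-point difference in hospitalization. Neither the size nor the power is right for the inputs given. The missing direction matters too, because it alone moves the requirement by about half (948 v 1,452 in total).

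**Working it through.** **Inputs, all from the sample size section.** Two-sided alpha 0.05 (z = 1.960); power 0.80 (z = 0.8416); equal arms (946 × 2 = 1,892); hospitalization 10%; difference d = 0.05.

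The 10% can be read three ways: as one arm's rate with the other lower (10% v 5%), as one arm's rate with the other higher (10% v 15%), or as the average over both arms (7.5% v 12.5%).

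**Formulas.** With p̄ the mean of the two proportions, the uncorrected size per arm is

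n = [1.960·√(2p̄(1−p̄)) + 0.8416·√(p₁(1−p₁) + p₂(1−p₂))]² / d²

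and the continuity-corrected size per arm is

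n_c = (n/4)·[1 + √(1 + 4/(n·d))]².

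**Step 1: find the protocol's formula from the other two proportion bullets.**

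| Bullet | Rates | n | n_c | Stated |
|---|---|---|---|---|
| Referral | 20% v 26% | 771.1 | 804.05 | 804 |
| Mortality | 7.5% v 4.2% | 792.8 | 852.3 | 854 |

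The corrected formula fits; the uncorrected one does not. The common short form n + 2/d fits about as well: 771.1 + 33.3 = 804.4 for referral and 792.8 + 60.6 = 853.4 for mortality.

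**Step 2: try to reproduce 946 for hospitalization.** For 10% v 5%, p̄ = 0.075:

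- 1.960·√(2·0.075·0.925) = 0.7301
- 0.8416·√(0.09 + 0.0475) = 0.3121
- n = (1.0422)²/0.0025 = 434.4
- n_c = (434.4/4)·[1 + √(1 + 4/21.72)]² = 473.6

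All three readings, rounded up:

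| Rates | n per arm (total) | n_c per arm (total) | 1,892 ÷ corrected total |
|---|---|---|---|
| 10% v 5% | 435 (870) | 474 (948) | 2.00 |
| 7.5% v 12.5% | 564 (1,128) | 604 (1,208) | 1.57 |
| 10% v 15% | 686 (1,372) | 726 (1,452) | 1.30 |

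The largest of these, 726, is 23% below 946. Unpooled variance (432, 562, 683) and the arcsine form (424, 557, 681) move further away.

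**Step 3: what 946 per arm would deliver.** For the corrected power, n in the power formula is replaced by (946 − 1/d)²/946 = 926²/946 = 906.4.

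| Rates | Power, uncorrected | Power, corrected |
|---|---|---|
| 10% v 5% | 98.5% | 98.2% |
| 7.5% v 12.5% | 95.3% | 94.4% |
| 10% v 15% | 90.9% | 89.7% |

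Solving for the difference from 10% that 946 per arm detects with 80% power gives 3.6 points down or 4.3 points up (corrected), or 3.5 and 4.2 (uncorrected).

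**Step 4: which inputs come near 946?**

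- The total for 10% v 5%: 2 × 473 = 946. This needs 473.6 rounded down; rounded up, the total is 948.
- The per-arm size for 15% v 20%: 944.9 corrected, or 905.4 + 40 = 945.4 by the short form, which rounds up to 946.
- The per-arm size for 10% v 15% with one further input changed: 918 to 957 at power 0.90, 955 at alpha 0.05/3 with correction, or a dropout allowance of about 25% to 30%.

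The first does not give a per-arm size, and each of the others needs an input that the protocol does not state.

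**The case against.** The strongest points on the other side concern the cause and the stakes, not the arithmetic.

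**Cause.** A reader might infer that a total of 946 was mistaken for a per-arm size and doubled again. The documents do not support going that far. That account needs a downward rounding, whereas 15% v 20% gives 945 to 946 per arm directly, with a correction that fits the other two bullets. Equally, 15% v 20% might be a leftover from a higher assumed rate, but nothing in the protocol shows it. The cause stays open, and the non-reproduction does not depend on it.

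**Size of the error.** It is tempting to say that the figure is wrong by a factor of 2. That holds only for 10% v 5%. The neighbouring bullets do not settle the direction: referral is computed upward (20% to 26%), while the mortality figure fits a downward difference (7.5% to 4.2%). If hospitalization was meant to go up, the excess is about 30%.

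**Stakes.** A reader might infer that the trial is twice as large as it needs to be. The protocol does not say that 1,892 is the enrolment target. If the other bullets stand, the largest remaining total is 1,708, so the maximum falls by 184 (about 10%), not by half. The error is also conservative, since hospitalization has more power than claimed. These points limit the consequence. They do not make the sentence correct.

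**Conclusion.** The concern holds. With the stated level, power, rate and difference, 946 per arm cannot be reproduced. The need is 474 to 726 per arm with the continuity correction, or 435 to 686 without it, depending on how the 10% and the unstated direction are read. The stated size overstates the need by about 30% (10% v 15%) to a factor of 2 (10% v 5%), and the true power at that size is about 90% to 98%, not 80%.

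This rests on equal allocation and on no unstated dropout or multiplicity allowance. The corrected figures also rest on the formula inferred from the referral and mortality bullets, but the failure to reproduce does not, because no standard variant reaches 946. Hospitalization is not underpowered. What is wrong is the largest of the five listed totals, its stated power and the difference it is said to detect.

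**What to change.** In the hospitalization bullet, state both assumed proportions and the direction, name the formula, and make the size match:

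- 10% v 5%: 474 per arm, 948 in total.
- 7.5% v 12.5%: 604 per arm, 1,208 in total.
- 10% v 15%: 726 per arm, 1,452 in total.

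If 946 per arm is to be kept, do one of two things. Either state what it detects from 10% with 80% power (about 3.6 points down or 4.3 points up, continuity-corrected; 3.5 and 4.2 uncorrected), or, if 15% v 20% was the real input, correct the assumed 10% rate and its rationale. If another input was used, such as a higher power, a split alpha or a dropout allowance, state it.

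The cost is one corrected sentence in the protocol. No extra patients are needed on any of these routes.

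### The 7.5% mortality and 10% hospitalization assumed for the same enrolled patients are mutually implausible and unreconciled, so the stated 80% mortality power rests on an unsupported rate

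*Protocol*

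**What the plan says.** All the figures are in the Protocol, section Sample size for primary outcome indicators.

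- Method: "we used a two-sided test of independent proportions with the statistical parameters of alpha 0.05, beta 0.2, and power of 0.8".
- Hospitalization: the cited Honduran study "identified a 25% hospitalization rate in the general population, prior to vaccine availability". For this trial: "We estimate that 10% of all enrolled patients will be hospitalized, taking into account increasing vaccination coverage and the high risk status" of those enrolled. The sample size follows: "The ability to detect a 5% absolute difference in hospitalization rates between arms requires 946 participants per arm".
- Mortality: "Given an estimated mean mortality of 7.5% among the enrolled population, a per arm sample size of 854, and a total sample of 1708", which "is powered to detect a difference in mortality rate of 3.3% between groups". The reference figure is: "The mean mortality rate among people with COVID in Honduras is 2.8% among the general population". The reason given for going higher is that participants will be older and have more comorbidity. No source is given for 7.5%.

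The Indicators section stars mortality as a primary outcome and does not limit it to deaths in hospital. Project Population describes the patients as higher-risk, but clinically stable and fit for home care.

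**The concern.** Two bullets of one section describe the same patients, and the adjustments run in opposite directions. Hospitalization goes down from 25% to 10%, allowing for vaccination and high risk together. Referral is also lowered, to 20%, because of vaccination. Mortality goes up from 2.8% to 7.5% for age and comorbidity, and vaccination is not mentioned. The result is a planned number of deaths close to the planned number of admissions, in people who are stable at entry and phoned daily.

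At stake is the stated power for a starred primary outcome. If deaths are much rarer than 7.5%, a trial of this size has well under 80% power for the same proportional benefit, and a null mortality result could be read as more informative than it is.

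**Working it through.** **1. The plan's own figure.** Inputs: two-sided alpha 0.05, power 0.80, p1 = 0.075, p2 = 0.075 − 0.033 = 0.042, d = 0.033. Equal arms are assumed.

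n = [1.960·√(2p̄(1−p̄)) + 0.842·√(p1(1−p1) + p2(1−p2))]² / d², with p̄ the mean of the two rates, gives 792.8.

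Continuity correction: n_c = (n/4)·[1 + √(1 + 4/(n·d))]² = 852.3, so 853 per arm against 854 stated. The figure is reproduced. The same corrected formula gives 804.05 for referral at 20% v 26% (804 stated), so the correction appears to be the method used. Other readings of 7.5% do not fit: 7.5% v 10.8% needs 1,257 corrected, and 9.15% v 5.85% (7.5% as the mean of the arms) needs 1,059.

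**2. Deaths per admission.**
- 7.5/10 = 0.75. In an arm of 854 that is 0.075 × 854 ≈ 64 deaths and 0.10 × 854 ≈ 85 admissions.
- If 7.5% and 4.2% are the arm rates, overall mortality is (7.5 + 4.2)/2 = 5.85%, and 5.85/10 = 0.585.
- The Protocol does not give the share of deaths that follow admission. Taking 7.5% and assuming shares of 100%, 75% and 50%, fatality among admitted patients is 75%, 56% and 37.5%. At 50%, 3.75% of all participants would die without being admitted.
- For orientation only, the cited general-population rates give 2.8/25 = 0.11.

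**3. The 10% itself.** With the corrected formula, 10% v 5% needs 474 per arm and 10% v 15% needs 726. The stated 946 is close to 15% v 20%, which needs 945. With 15% or 20% hospitalized, 7.5% mortality gives 0.50 or 0.375 deaths per admission.

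**4. Power at lower mortality.** The planned relative reduction is 3.3/7.5 = 44%, so p2 = 0.56·p1. Corrected power comes from inverting the correction, m = N·[1 − 1/(N·d)]², and putting m into the uncorrected power formula. N = 854 is the mortality calculation's size; N = 946 is the largest per-arm size stated.

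| Mortality, comparison arm | Other arm | Power, 854 per arm | Power, 946 per arm | Per arm for 80% |
|---|---|---|---|---|
| 7.5% | 4.20% | 80% | 84% | 853 |
| 6% | 3.36% | 69% | 74% | 1,079 |
| 5% | 2.80% | 60% | 65% | 1,304 |
| 4% | 2.24% | 50% | 54% | 1,643 |
| 2.8% | 1.57% | 35% | 39% | 2,368 |

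**5. Holding 3.3 points fixed instead.** Corrected power at 854 then rises, to 90% at 6%, 96% at 5% and 99% at 4%. The effect needed becomes 3.3/6 = 55%, 3.3/5 = 66% and 3.3/4 = 82.5% relative. At 2.8% a 3.3-point reduction is impossible.

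**The case against.** The best defence is that the two rates do not strictly contradict each other. Deaths do not exceed admissions. Mortality covers all participants, and the Protocol itself foresees limited advanced care, oxygen given outside hospital, and referred patients who may not reach care. Deaths without admission are therefore possible. That stands: a reader might infer that the plan implies 75% of admitted patients die, but this needs every death to follow an admission, which the Protocol does not say. It does not, however, say that many deaths would occur outside hospital, so the pair stays unexplained.

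It can also be said that the fault may lie in the 10%. That stands in part. The 946 does not follow from 10%, and a higher hospitalization rate brings the ratio down, though only to 0.375 to 0.50 with 15% to 20% hospitalized.

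A third defence is that an older, sicker population should die more often than the general 2.8%. That is reasonable and is the Protocol's stated reason. It supports a rate above what a general population with the same vaccination coverage would have; it does not by itself support 7.5%.

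Finally, multiplying 2.8/25 by 10% would suggest about 1.1% mortality. The documents do not support using that as a scenario. The 2.8% comes from a regional information system and the 25% from a study in one metropolitan area, with no sign that their denominators match, and the result would put this high-risk group below the general population.

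**Conclusion.** The point holds as one about unreconciled assumptions. For the same stable, high-risk patients the plan assumes 0.585 to 0.75 deaths per admission, depending on how 7.5% is read, and gives no explanation. The sample-size arithmetic for mortality is sound on its inputs; a reader might take the 854 to be a miscalculation, and it is not. What is unsupported is the 7.5%, and the 80% power depends on it.

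If the 44% relative reduction is kept, power at 854 per arm falls to between about 69% (6% mortality) and 35% (2.8%). These losses rest on holding the relative effect. Under a fixed 3.3-point difference nominal power rises, but the required effect becomes implausibly large and then impossible. The documents do not fix the true rate, so the range shows sensitivity and is not a forecast.

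A reader might go further and conclude that mortality must be dropped as a powered primary outcome. The evidence does not compel that; it calls for a justified rate and an honest display of power.

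**What to change.** In Sample size for primary outcome indicators:

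1. State one set of hospitalization and mortality rates for the enrolled population, each with its source and with vaccination, age and comorbidity treated alike. If many deaths without admission are expected, say so and give the share assumed.
2. Check the 10% in the same step, and state the two hospitalization rates behind 946 per arm.
3. State the two mortality rates behind 854 per arm, and that a continuity correction was used if so.
4. Show mortality power at the planned sample size over about 2.8% to 7.5%, as in the table above, saying whether the relative or the absolute effect is held.
5. Present the mortality comparison with a confidence interval and refer to that power range when interpreting it.

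The cost is a wording change and a less favourable stated power. No extra patients or data are needed.

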## Data analysis

The primary analysis will provide unadjusted and adjusted differences between arms/strategies based on the covariates listed. We will perform additional subgroups analyses, specifically examining age, sex, comorbidities, baseline clinical features, and timing of the interventions. Qualitative analyses will be conducted by trained researchers using Excel to organize data, given the limited sample sizes. Research analysis will adhere to the Sex and Gender Equity in Research (SAGER) guidelines including reporting representativeness, presenting disaggregated results regardless of positive or negative outcome, withdrawal/attrition rates, and implications of reported gender on study results.

## Training and Qualifications of Personnel

Study staff will be trained to enter study data directly into electronic tablets. Study staff will be trained in enrollment and consent procedures, administration of study entry questionnaires, providing home-based care and how to obtain information about COVID-19 outcomes from patients, their family members and/or facilities to which they are referred for high levels of care. They will also be trained in research ethics and database management.

## Risks and Benefits to Participants

### *Risks to confidentiality*

There is a low risk that study databases could be accessed, and patient information obtained. However, all data maintained in the database will be de-identified with only the PI, project manager, and data manager able to access the key to de-identify data. The patient monitoring form does not include sensitive questions that would be expected to be stigmatizing or cause emotional distress. Further, we will ensure participants know that they do not have to answer any questions that make them uncomfortable. Only study personnel will be allowed to review this information. All data will be entered directly into the electronic database and no paper records will be maintained. We will adhere to best practice mechanisms to ensure data security as described below. Evaluation staff will receive training in confidentiality and the protection of personally identifiable information.

### *Risk of exposure to study staff*

There is a low risk that study staff could potentially be infected while interacting with study participants or could potentially be infectious and transmit to study participants. Study staff will follow all infection prevention guidelines, including mask-wearing, hand hygiene, and social distancing. Any staff traveling between Honduras and the United States will be required to be vaccinated against SARS-CoV-2.

### *Reporting of potential adverse events*

Given the nature of the study, the risk of adverse events related to study participants is low. However, the project will monitor for unexpected or unintended adverse events related to patient safety by ensuring all project staff are trained on the identification and reporting of these events. Reporting will be to the Project Manager and these will be reported at a minimum monthly, or more frequently as PI requests, to the PI. Serious adverse events will also be reported to the respective Honduras, CDC, and Mass General Brigham IRB committees.

### *Benefits*

Individual participants will benefit by receiving an HBC kit. They will also receive follow-up from a medical worker which could help to more rapidly identify decompensation and facilitate referral to a higher level of care when necessary, which could lead to improved outcomes. There will also be societal benefits. Results will be shared with policymakers at the Ministry of Health and COVID-19 Taskforce, which can be used to inform and improve policies and programs for COVID-19 HBC and for HBC in general.

